**Fig 1 pone.0286816.g001:**
[figure not shown]
Conceptual framework of explanatory sequential mixed methods study design on predictors of depressive symptoms among men who have sex with men (MSM) living with HIV. Abbreviations: HIV, Human Immunodeficiency Virus; HAART, Highly Active Anti-Retroviral Therapy; CD4, Clusters of Differentiation 4.

### Settings

Both study phases will be conducted in ten Primary Care Clinics in Selangor with the highest number of MSM living with HIV registered. Selangor has been chosen as the study location as a previous study shows a high prevalence of depressive symptoms among MSM in Selangor (10). Quantitative data collection was conducted from March 2022 to February 2023, while qualitative data collection is from March 2023 to April 2023.

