**Methods:**

The study has ethical approval from the Medical Research Ethics Committee (MREC) of the Ministry of Health (MOH) NMRR ID-21-02210-MIT. This study will apply an explanatory sequential mixed methods study design. It comprised two distinct phases: quantitative and qualitative study design for answering the research questions and hypothesis. This study will randomly recruit 941 MSM living with HIV in the quantitative phase, and at least 20 MSM living with HIV purposively will be selected in the qualitative phase. The study will be conducted in ten public Primary Care Clinics in Selangor, Malaysia. A self-administered questionnaire will gather the MSM’s background and social, psychological, and biological factors that could be associated with depressive symptoms. For the quantitative study, descriptive analysis and simple logistic regression will be used for data analysis. Then, variables with a P value < 0.25 will be included in multiple logistic regression to measure the predictors of depressive symptoms. In the qualitative data collection, in-depth interviews will be conducted among those with moderate to severe depressive symptoms from the quantitative phase. The thematic analysis will be used for data analysis in the qualitative phase. Integration occurs at study design, method level, and later during interpretation and report writing.

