Depression among MSM has significant effects on public health. Depression affects physical, educational, social, economic, psychological, and short- and long-term health effects for MSM living with HIV [12]. The presence of depressive symptoms may reduce an individual’s motivation to engage in self-care and thus increase the likelihood of risky behavior and suicide [13, 14]. Among MSM living with HIV that have compulsive sexual behavior, having sex can become an alternative strategy to cope with negative emotions such as loneliness, anxiety, and stress [15]. Regarding viral load suppression, depression is a risk factor for ‘imperfect’ antiretroviral therapy (ART) adherence among MSM living with HIV that could jeopardize the Treatment as Prevention (TasP) strategy [16]. More importantly, the co-occurrence of HIV and depression was related to adverse health outcomes, such as low quality of life and deterioration of disease conditions [17].

A complicated combination of biological, psychological, and social variables could cause depression [3]. Therefore, the biopsychosocial approach has been used to structure guidelines, is used clinically, and discusses person-centered care, which can improve patient outcomes [18, 19]. The factors that increase depression among MSM living with HIV include younger age, unemployment, smoking, externalized HIV stigma, not being on ART, lack of self-efficacy, and low social support [20]. In addition, MSM are prone to mental health problems owing to sexual minority stress, homophobia, persecution based on sexual orientation, and stigmas that prevent healthy behavior [21, 22].

Addressing the mental health concerns of individuals living with HIV is essential to providing quality HIV care [9]. In many low and middle-income countries, MSM have fewer resources and are more likely to be hidden and stigmatized, compounding HIV acquisition and transmission risks and limiting access to the most basic services [23]. Continuing research, additional resources, political will, policy change, institutional transformation, community participation, and strategic planning and programming will be required to combat the increasing prevalence of depression among MSM living with HIV.

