### General objective

To determine and explain the predictors of depressive symptoms among MSM living with HIV in Selangor.

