### Specific objectives for quantitative study

To determine the prevalence of depressive symptoms among the MSM living with HIV in Selangor.To describe the distribution of biological, psychological, and social factors of depressive symptoms among MSM living with HIV in Selangor.To determine the association between biological, psychosocial, and social factors and depressive symptoms among MSM living with HIV in Selangor.

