### Inclusion and exclusion criteria

The inclusion criteria were: (1) Malaysian; (2) able to read and understand the Malay or English language; (3) men self-identified as having sex with men based on the clinic database; and (4) men with HIV diagnosis. The exclusion criteria were: (1) those aged less than 18 years old and (2) those known to have psychiatric disorders.

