### Sampling methods

A proportionate random sampling was applied. The HIV databases from each clinic were obtained from the Selangor State Health Department to look for the list and the total number of patients in each clinic. Then, the required number of MSM in each clinic was calculated based on proportion to get 941 MSM. To build trust with the MSM and ease the data collection process, the researchers engaged with HIV clinic nurses and appointed them as research nurses. Next, the lists of MSM in each clinic were obtained to screen them for inclusion and exclusion criteria. Based on the screened name list of MSM in each clinic, random sampling is conducted to select the required number of MSM using a randomizer application. New master lists of selected MSM were extracted in an Excel sheet that contained their personal information, clinical information, and the clinic appointment date to remind the researcher to ask for written consent and to collect the data when the MSM visit the clinic. From the list, the researcher will create and insert a code to replace the MSM’s names on the questionnaire and during the in-depth interview.

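### The prevalence objective is stated for MSM living with HIV in Selangor, but the design samples only eligible men listed as MSM at ten selected public clinics

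*Protocol article*

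**What the plan says.** The target is set without qualification. The General objective is "To determine and explain the predictors of depressive symptoms among MSM living with HIV in Selangor", and the first item under Specific objectives for quantitative study is "To determine the prevalence of depressive symptoms among the MSM living with HIV in Selangor". The other two quantitative objectives, on distribution and association, name the same population.

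The design narrows that population in several steps:

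- **Sites.** Settings places both phases in "ten Primary Care Clinics in Selangor with the highest number of MSM living with HIV registered". The Abstract (Methods) adds the sector: "The study will be conducted in ten public Primary Care Clinics in Selangor, Malaysia".
- **MSM status.** Inclusion and exclusion criteria admits "men self-identified as having sex with men based on the clinic database".
- **Other eligibility limits.** The same section requires Malaysian nationality and the ability to read Malay or English. It excludes "those aged less than 18 years old and (2) those known to have psychiatric disorders".
- **Selection.** Under Sampling methods, "Based on the screened name list of MSM in each clinic, random sampling is conducted", with numbers allocated to clinics in proportion.
- **Contact.** Under Study processes, selected men are approached at clinic appointments or visits.

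The only design limit stated in the Discussion is that a cross-sectional study cannot establish temporal order. Transferability is discussed for the qualitative phase only.

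**The concern.** A prevalence is a statement about a defined population. Here the population named in the objective and the population that can enter the sample differ. A man registered at any other Selangor clinic, or not recorded as MSM, has no chance of selection. The same holds for a man removed at screening because of a known psychiatric disorder. No increase in sample size and no reweighting among the ten clinics brings such men back.

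The psychiatric exclusion deserves particular attention because it bears directly on the outcome. A prevalence of PHQ-9 scores of 10 or more in men without a known psychiatric disorder is a different quantity from the prevalence in all MSM living with HIV.

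If the objective is reported as worded, the result will be read as a state figure. Its confidence interval will reflect sampling error only. The Discussion presents the point prevalence in a large sample as one of the main values of the design, and the Introduction expects the findings to inform public health policy and programmes, so the population to which the number belongs matters.

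**Working it through.** **1. The plan's own figure.** Sample size calculation uses P1 = 0.55 and P2 = 0.45 with z = 1.96. Power is not stated in words; 80% (z = 0.8416) is assumed here.

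n per group = [1.96 × √(2 × 0.5 × 0.5) + 0.8416 × √(0.55 × 0.45 + 0.45 × 0.55)]² / 0.10² = 391.3, rounded up to 392.

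392 × 2 = 784, and 784 × 1.2 = 940.8, rounded to 941.

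The stated 392, 784 and 941 are reproduced. They set the precision of the estimate and are silent on coverage, so rewording the objective leaves them unchanged.

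**2. Stated target against sampled population.**

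| Feature | Objectives | Design |
|---|---|---|
| Place | Selangor | Ten public primary care clinics in Selangor, chosen for the most registered MSM living with HIV |
| MSM status | Any MSM | Recorded as MSM in the clinic database |
| Nationality, age, language | Not limited | Malaysian, 18 or over, reads Malay or English |
| Psychiatric history | Not limited | Known psychiatric disorder excluded |
| Contact | Not limited | Attends during data collection |

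The clinic limit comes from the setting and the sampling frame; the other limits in the table, apart from contact, are eligibility criteria. Every row makes the sampled group narrower than the stated one.

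**3. Sampling error the interval would show.** Half-width = 1.96 × √(p(1 − p)/n), with n = 784 and simple random sampling. The Introduction cites a prevalence of 43% to 58%.

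- p = 0.43: 1.96 × √(0.43 × 0.57/784) = 0.0347
- p = 0.58: 1.96 × √(0.58 × 0.42/784) = 0.0345

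That is about 3.5 percentage points.

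**4. Coverage error the interval would not show.** Let c be the share of the stated target population that the design can reach, and d the absolute difference in prevalence between men it can and cannot reach. The absolute error is (1 − c) × d. The documents give neither c nor d, so the grid below is an illustration under assumed values, in percentage points.

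| Assumed coverage c | d = 5 | d = 10 | d = 20 |
|---|---|---|---|
| 90% | 0.5 | 1.0 | 2.0 |
| 70% | 1.5 | 3.0 | 6.0 |
| 50% | 2.5 | 5.0 | 10.0 |
| 30% | 3.5 | 7.0 | 14.0 |

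Coverage error equals the 3.5-point half-width when the unreached share is 3.5/d: 70% at d = 5, 35% at d = 10 and 17.5% at d = 20. The error can therefore be negligible or several times the sampling error, and the documents do not say which.

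**The case against.** The restriction is disclosed. The sites, the reason for choosing them, the database criterion and the sampling frame are all stated, and Settings describes Selangor as the study location, so the phrase in the objectives could be read as naming a place and not a population. The Conclusion of the Abstract claims no state figure. Clinic registers are a standard frame for a population that is hard to reach, and the ten clinics with the most registrations capture more registered men than any other ten would. A journal article may also leave a fuller discussion of limitations to the results paper.

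Much of this stands. It shows that the choice of frame is defensible and that sampling within it is sound. It does not settle the wording: the objective is to determine a prevalence among men in Selangor, and nothing in the article narrows it.

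A reader might go further and infer that men who have not disclosed to the clinic have the highest stigma scores, so that the range of stigma is cut at the top and its association with depressive symptoms is weakened. The documents do not support that. The remark that "MSM have fewer resources and are more likely to be hidden and stigmatized" is a general statement about many low- and middle-income countries and does not concern disclosure to HIV clinics in Selangor. The instrument measures HIV-related stigma, and a man absent from the MSM list may have withheld his sexual behaviour from a clinic that already knows his HIV status. No score distribution is available. Moreover, selection on an exposure alone costs precision but does not by itself bias an odds ratio.

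**Conclusion.** The point holds as a mismatch between the claim and the sampled population. Sampling within the ten clinics' lists is random and supports inference to eligible, attending men on those lists. It does not support a prevalence for all MSM living with HIV in Selangor. The overreach is mainly a matter for the prevalence objective; associations are likely to be less affected by who is covered.

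The size and direction of the error are unknown. The range of 0.5 to 14 points rests entirely on assumed coverage of 90% to 30% and assumed differences of 5 to 20 points, and the 3.5-point comparison assumes 784 respondents and simple random sampling. A reader might infer from the adverse cells that the prevalence is biased by several points, or biased downwards because men with known psychiatric disorders are left out. Neither is established: the article gives no counts or scores for the men outside the frame, and the different uncovered groups could pull in different directions.

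**What to change.** Restate the prevalence objective and the conclusions for the population actually sampled. For example: Malaysian men aged 18 or over who can read Malay or English, have no known psychiatric disorder, are recorded as MSM in the HIV databases of the ten public primary care clinics in Selangor with the most registered MSM living with HIV, and attend those clinics. The psychiatric exclusion must appear in that wording; without it the claim is still wider than the sample. Do not present the prevalence as a state figure.

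If the State Health Department's counts allow it, report the share of Selangor's registered MSM living with HIV that the ten clinics hold. Sampling methods shows that the department supplied databases for the clinics, but not that counts or records from non-participating clinics are available, so this should be conditional. A comparison of clinical data with other clinics need not be required: access is not established, and it would say nothing about men not recorded as MSM.

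The cost is wording and, where possible, one administrative count. No recruitment, sample size or model changes. The downside is a narrower claim.

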### Inclusion and exclusion criteria

The inclusion criteria were: (1) Malaysian; (2) able to read and understand the Malay or English language; (3) men self-identified as having sex with men based on the clinic database; and (4) men with HIV diagnosis. The exclusion criteria were: (1) those aged less than 18 years old and (2) those known to have psychiatric disorders.

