## Abstract

**Background:**

Depression is the most common psychiatric disorder reported among patients living with Human Immunodeficiency Virus (HIV), resulting from the intricate combination of biological, psychological, and social factors. Biopsychosocial factors can significantly impact the psychological well-being of men who have sex with men (MSM) living with HIV through social stigma, access and compliance to care, economic insecurity, relationship difficulties, and risky behavior. Compared to MSM without HIV, MSM living with HIV were more likely to be depressed. Despite specific vulnerabilities and health needs, MSM living with HIV remain understudied and underserved in Malaysia owing to legal, ethical, and social challenges.

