## Introduction

Globally, over 264 million individuals suffer from depression, which is characterized by constant sorrow and a loss of pleasure or interest in activities that were before satisfying or enjoyable [1]. Depressive symptoms are generally known by the SIGECAPS mnemonic: sleep disorders (increased or decreased); interest shortfall; guilt (worthlessness, hopelessness, regret); energy shortage; concentration deficiency; appetite disorder (decreased or increased); psychomotor sluggishness or agitation; and suicidality. The presence of four SIGECAPS symptoms plus depressed mood or anhedonia suggests depression, and further screening should be considered [2]. Depression is distinct from regular mood swings and quick emotional reactions to ordinary stresses. It can be a serious health issue, mainly when persistent and moderate or severe [3]. Among persons with Human Immunodeficiency Virus (HIV) infection, depression is the most commonly documented psychological condition [4]. In a systematic review and meta-analysis, the pooled prevalence of depression among men who have sex with men (MSM) worldwide was 35%. Further continent analysis showed that Asian MSM had the highest pooled prevalence of depression at 37% [5]. Compared to MSM without HIV, MSM living with HIV were more likely to be depressed, with 43% to 58% depression prevalence based on the previous systematic review and study [6, 7].

By 2030, MSM are projected to account for the largest share of prevalent HIV infections in Malaysia, according to Asian Epidemic Modelling (AEM) [8]. In Malaysia, there was an estimated 220,000 MSM population with 21.6% HIV prevalence, making it the highest among other key populations: female sex workers (6.3%), transgender women (10.5%), and people who inject drugs (13.5%) [9]. Regarding depression, to date, the study involving MSM in Malaysia with the highest number of participants was conducted involving 622 mixed MSM with and without HIV status, where 60.8% of them had Center for Epidemiologic Studies Depression (CES-D) scores of ≥ 16, indicating major depression symptoms [10]. However, in this study, the Patient Health Questionnaire-9 (PHQ-9) is utilized since it is half the length of the CES-D, is readily administered and scored, and is increasingly used across various patient groups in research and clinical settings [11].

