### Statistical methods and analysis

#### Sample size calculation

The sample was chosen based on a study by Perdue et al. (2003) [37], as this study gave the highest number of samples and the most feasible numbers to execute this research within the time frame.

P1 = 0.55 (Proportion of depression among MSM with education below college)

P2 = 0.45 (Proportion of depression among MSM with education level at college or higher)

$$\text{n}=\;\frac{\left\{1.96\;\surd 2\left(0.55\right)\;\left(1-0.55\right)\;+\;0.62\surd \;\left(0.55\left(1-0.55\right)\right)\;+0.45\left(1-0.45\right)\right\}2}{\left(0.55-0.45\right)2}$$

n = 392

Considering adjustment for comparison between 2 groups

= 392 x 2

= 784

Considering adjustment for non-response of 20%

= 784 + [(0.2) (784)] = 941

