#### Data analysis for quantitative study

Data will be collected and analyzed using the IBM Statistical Package for Social Science (SPSS) version 25, involving descriptive and inferential statistics. The descriptive statistics will describe the MSM’s characteristics: mean, standard deviation, mode, median, interquartile range, and percentage. Cross-tabulation and frequency counts will be used to assess the demographic items and the MSM’s responses to survey scales. The data analysis utilizes both univariate and multivariate statistical methods. Simple logistic regression will be used to measure the associations between independent and dependent variables. A less rigorous threshold, such as a P-value < 0.25, should be applied to prevent omitting crucial variables from a model due to stochastic variation [38, 39]. Therefore, variables with a P value < 0.25 will be included in multiple logistic regression to measure the predictors of depressive symptoms. The binary outcomes of depressive symptoms will use a cut-off score ≥10. The scores of 0 to 9 represent none to subthreshold depression, and a score of 10 and above represents a patient’s spectrum to possible major depression [40]. The level of significance at 0.05 and 95% confidence interval (CI) will be used to yield a significant result.

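### Men with a known psychiatric disorder, diagnosed depression included, are removed before sampling, yet prevalence and predictors are claimed for all MSM living with HIV in Selangor

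*Protocol article*

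**What the plan says.** Four parts of the protocol article bear on this.

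- **Eligibility.** The section on inclusion and exclusion criteria lists "those known to have psychiatric disorders" as an exclusion. It gives no reason and does not exempt depressive disorders. The Background of the Abstract itself names depression as the psychiatric diagnosis reported most often in people with HIV.
- **Sampling methods.** The exclusion acts on the sampling frame: "the lists of MSM in each clinic were obtained to screen them for inclusion and exclusion criteria". The random selection is then made from the screened list.
- **Specific objectives for quantitative study.** The first objective is "To determine the prevalence of depressive symptoms among the MSM living with HIV in Selangor". The third is "To determine the association between biological, psychosocial, and social factors and depressive symptoms among MSM living with HIV in Selangor". Neither is limited to men without a diagnosis, and the General objective is not limited either.
- **Outcome.** The analysis section dichotomises the PHQ-9 and explains that "a score of 10 and above represents a patient’s spectrum to possible major depression".

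The Discussion names the lack of temporal order as the limitation of the cross-sectional design. It presents the point prevalence in a large sample as a strength, without mentioning the exclusion.

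**The concern.** A known psychiatric disorder is a marker of the outcome under study. Men whose depression has already been recognised cannot enter the frame, so neither random selection nor a larger sample brings them back. The interviews draw on the same men, so this group is absent from the second phase too.

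Two results are at stake. The first is the prevalence figure, which is meant to inform services and policy for the whole population but leaves out men already known to be ill. The second is the set of odds ratios. Some of the questionnaire's factors, possibly family history of psychiatric disorder, education or income, may affect whether a depressed man has been diagnosed. For such factors the exclusion may remove depressed men unevenly across levels of the factor.

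**Working it through.** **Inputs from the article.** Background prevalence: "MSM living with HIV were more likely to be depressed, with 43% to 58% depression prevalence" (Introduction). For an illustrative odds ratio: 0.55 (education below college) and 0.45 (college or higher), from the sample size calculation. These two are subgroup proportions, so I do not use either as a population prevalence. The calculation gives 392 per group, and 392 × 2 = 784; I use 784 only for sampling error.

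**Inputs not in the article, assumed.** k, the share of otherwise eligible men excluded for a known disorder; q, the share of those men who would score PHQ-9 ≥ 10; and the exclusion probabilities used for the odds ratio. The plan has no figure of its own for this bias to reproduce.

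**Prevalence.** With P the prevalence in all men:

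observed = (P − kq)/(1 − k), so the shift is k(P − q)/(1 − k).

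It is downward if q > P, zero if q = P and upward if q < P.

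| k | P = 43%, q = 0.7 | P = 43%, q = 0.9 | P = 58%, q = 0.7 | P = 58%, q = 0.9 |
|---|---|---|---|---|
| 5% | 41.6% | 40.5% | 57.4% | 56.3% |
| 10% | 40.0% | 37.8% | 56.7% | 54.4% |
| 20% | 36.25% | 31.25% | 55.0% | 50.0% |

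Example: (0.43 − 0.10 × 0.7)/0.90 = 0.36/0.90 = 40.0%.

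Reverse case, excluded men mostly well controlled: k = 10%, q = 0.3 gives (0.43 − 0.03)/0.90 = 44.4%.

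For scale, the 95% half-width near 50% with 784 respondents is 1.96 × √(0.25/784) = 3.5 points. At k = 10% and q = 0.7 to 0.9 the shift is −3.0 to −5.2 points for P = 43% and −1.3 to −3.6 points for P = 58%. It may be smaller or larger than the sampling error, depending on values that the article does not give.

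**Odds ratios.** Let s1 and s0 be the exclusion probabilities among depressed men with and without the factor, and t1 and t0 the same among non-depressed men:

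observed OR = true OR × [(1 − s1)(1 − t0)]/[(1 − s0)(1 − t1)].

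The true OR from 0.55 v 0.45 is (0.55 × 0.55)/(0.45 × 0.45) = 1.49.

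- Exclusion depends on depression only (s1 = s0 = 10%, t1 = t0 = 2%): the multiplier is 1 and the OR stays at 1.49.
- Depressed men with the factor are diagnosed more often (s1 = 20%, s0 = 10%, t1 = t0 = 2%): 1.49 × 0.80/0.90 = 1.33.
- The reverse (s1 = 10%, s0 = 20%, t1 = t0 = 2%): 1.49 × 0.90/0.80 = 1.68.
- The factor changes exclusion equally in depressed and non-depressed men (s1 = t1, s0 = t0): the multiplier is 1 again.

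**From the observed figure back to all MSM.** P = (1 − k) × observed + k × q. With 40% observed and k = 10%, this is 36% + 10% × q: 36% at q = 0, 41% at q = 0.5 and 46% at q = 1. The full range is k wide, so the count of excluded men settles most of the matter.

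**The case against.** The restriction is openly stated, and short objectives are normally read together with the eligibility criteria; nationality, age and language are not repeated in them either. The criterion is also not the outcome itself. The PHQ-9 covers symptoms over two weeks, whereas an excluded man may be in remission, well treated, or have a disorder other than depression. Estimates for men without a known disorder remain valid.

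Much of this stands, and it limits what may be said. It does not remove the mismatch: unlike age or language, this criterion is a direct marker of the outcome, and the article offers point prevalence as a strength without the caveat.

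A reader might infer more than the article supports:

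- *That prevalence is certainly understated.* This requires q > P. It is the likelier case, but the article gives no information on q.
- *That odds ratios are distorted in a known direction, so that factors favouring diagnosis look protective.* Selection on depression alone leaves the OR unchanged. Exclusion of non-depressed men can offset the effect, and the direction differs by factor.
- *That the result cannot be set beside the 43% to 58% in the Introduction.* The eligibility rules behind those figures are not shown, and the article plans no such comparison. Comparability is unestablished rather than disproved.
- *That the screened lists already identify the men removed.* The sampling section says the lists were screened, but not that reasons for removal were kept.

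**Conclusion.** The mismatch between frame and objectives is real and can be read directly from the article. As planned, the study estimates the prevalence and predictors of depressive symptoms among MSM living with HIV without a known psychiatric disorder, not among all MSM living with HIV in Selangor.

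For the wider population, prevalence is likely too low if excluded men score ≥ 10 more often than average. The illustration of 43% observed as about 38% to 40% rests on assumed values (10% excluded, 70% to 90% of them positive) and reverses if most excluded men are well controlled. Odds ratios change only where diagnosis depends jointly on depression and the factor; the examples of 1.33 and 1.68 against 1.49 show a possible size, not an estimate. The mismatch should be corrected before results are reported, but the documents do not support a claim of large bias or of bias in a fixed direction.

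**What to change.** Quantitative data collection ran to February 2023, so the remedy lies in the reporting:

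1. Restate Objectives 1 and 3 and the conclusions as applying to MSM living with HIV without a known psychiatric disorder.
2. Report, for each clinic, how many otherwise eligible men were removed for this reason, where the screening records allow. If they do not, say so and treat k as unknown.
3. Give a sensitivity range for prevalence in all MSM, (1 − k) × observed + k × q, with q from 0 to 1 and 0.5 to 1 shown as the likelier part. Starting at 0.5 would leave out the case in which the bias reverses.
4. State in the Discussion that comparability with studies of unselected MSM is not established, and that odds ratios for factors linked to diagnosis may be affected in either direction.

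This needs wording, a count where records exist and one line of arithmetic, with no new participants. The downside is a narrower stated claim.
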